## Background

People with dementia prefer to live at home for as long as possible. In the Netherlands, it is estimated that 70% of people with dementia currently live in the community [1]. Many of these require 24-h support and care from a next of kin, typically a spouse, child, or other relative. Given that the number of people with dementia is expected to double over the next 20 years [2], growing numbers of relatives will be expected to provide care for a relative with dementia. However, caregivers themselves can experience high levels of burden and stress as a result of this role, ultimately leading to mental illness [3, 4] or early institutionalization of the dementia sufferer.

A prospective cohort study reported that half of all caregivers experienced excessive burden that increased over time and led to aggression, depression, anxiety, and poorer physical health [5]. Evidence also suggests that caregivers are at increased risk of serious illnesses and death [6]. Research on the effect of long-term caregiving has shown that it has long-term consequences. Indeed, in one study, psychological well-being among caregivers did not improve to levels comparable with those in non-caregivers after the person they cared for died or was admitted to a nursing home [7]. The high levels of burden to which a caregiver is exposed, typically through the poorer cognition and neuropsychiatric symptoms of the person with dementia [8], can also increase the risk of the care recipient being placed in a nursing home. Psychological morbidity in caregivers is also a predictor of mortality for people with dementia [9].

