### Randomization

Application will be by returning a signed informed consent form. Then, participant dyads (caregiver and patient) will be randomly assigned to either the intervention group or the control group by means of block randomization. The randomization sequence will be recorded in a separate document that will be unavailable to the research assistant responsible for participant enrolment.

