
#### Instruments used to assess the secondary outcomes in people with dementia

*The 12-item neuropsychiatric Inventory (NPI).* The main outcome of interest in the dementia group will be the NPI score. This is an informant-rated measure of the frequency and severity of neuropsychiatric symptoms, such as agitation, psychosis, depression and apathy in people with dementia, collected by interview with the caregiver. Higher scores indicate more severe neuropsychiatric symptoms [37].*Functional status.* We will assess this with an adapted version of the Katz Index of Independence of Activities for Daily Living (ADLs) and instrumental activities of daily living (IADLs), supplemented with a question concerning mobility (i.e., Katz-15; part of TOPICS-MDS). Caregivers will be asked if assistance is needed for six basic functions (e.g., bathing and dressing) and eight instrumental functions (e.g., telephoning and food preparation). Scores are binary (0 = independent, 1 = dependent), resulting in a potential total score between 0 and 15, with a higher score indicating a higher level of dependency [38].*Resource utilization.* Medical facility use and nursing home admission will be recorded from a week before baseline assessment and throughout the follow-up period (part of TOPIC-MDS). Use of services, such as home care, day care, and visits by case managers in the week before assessment will be recorded at baseline and at three and six months.*The Dementia Quality of Life Instrument (DQI).* This tool will be used to assess the quality of life of the people with dementia. It covers five health domains (i.e., memory, orientation, dependency, social activities, and mood); derived from the EQ-5D, it is effective at measuring quality of life in dementia of mild to moderate severity [39].*The Cohen-Mansfield Agitation Inventory-Community (CMAI-C) scale.* This is an informant-rated measure of the frequency of agitated behavior in people with dementia. Results are collected through interview with the caregiver and the score can range from 29 to 203, with higher scores indicating agitation that is more frequent [40].*The Geriatric Deterioration Scale (GDS).* This scale will be used to classify people with dementia based on the relative severity of their cognitive impairment and their functional status (range from 1 to 7), with higher scores indicating more severe dementia [41].

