### Statistical analysis

#### Sample size calculation

The sample size calculation was performed based on the results of the first Australian study [24]. In that study, 96 participant dyads were included, with 65 in immediate and waiting groups and 31 in a control group. Enrolling 144 couples, equally divided over intervention and control groups, should be sufficient to demonstrate a medium effect size (average 0.5) with a significance of 0.05 and a power of 0.8. The anticipated attrition rate is 10%.

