#### Outcome analysis

For the primary outcome, the change in the CarerQol-7D score from baseline to 3 months, a linear regression model will be developed to test the response variable for differences between the intervention and control groups, adjusting for the baseline outcome scores. We will perform a primary intention-to-treat analysis for the primary equation, which will be complemented with a secondary per-protocol analysis. The intention-to-treat population will include all information from participants randomized to each treatment arm, whereas the per-protocol population will only include information about those who completed the program to which they were allocated.

For the secondary outcome variables, multilevel analyses will be used to account for the dependency of the repeated measurements. A restricted, iterative, generalized least-squares algorithm will be used to estimate the regression coefficients, while the Wald test will be used to obtain *P* values for each regression coefficient. Linear or binary multilevel analysis will be conducted depending on the outcome measure. Subgroup analyses will be performed to assess the heterogeneity of treatment effects.

Assumptions of the normality and homogeneity of variance in the linear regression models will be assessed by inspecting normal probability plots and plots of standardized residuals compared with predicted values. If assumptions are not met, variables will be transformed to comply with the assumptions. If this does not yield acceptable distributions, variables will be dichotomized or we will use non-parametric statistical analyses. All statistical tests will be two-sided and will be required to meet the 5% significance criterion.

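### The primary regression could also prespecify baseline NPI and GDS as covariates: a nearly cost-free gain of modest, unknown size, not the repair of an error

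*Protocol article*

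**What the plan says.** Under Outcome analysis, the protocol article sets the primary model: change in CarerQol-7D from baseline to 3 months, in a linear regression testing for "differences between the intervention and control groups, adjusting for the baseline outcome scores". Baseline CarerQol-7D is the only covariate named. On the error rate it adds: "All statistical tests will be two-sided and will be required to meet the 5% significance criterion".

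Three other places bear on the point:

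- **Background.** The high burden on caregivers is said to arise "typically through the poorer cognition and neuropsychiatric symptoms of the person with dementia".
- **Outcome measures and Instruments.** Secondary outcomes, which include NPI and GDS, are measured at baseline as well as at 3 and 6 months. Of the NPI the article says: "The main outcome of interest in the dementia group will be the NPI score". The GDS grades severity from 1 to 7 on cognitive impairment and functional status together.
- **Randomization.** Dyads are "randomly assigned to either the intervention group or the control group by means of block randomization". No stratification factor is named.

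The Sample size calculation reads "Enrolling 144 couples, equally divided over intervention and control groups", which is held to be "sufficient to demonstrate a medium effect size (average 0.5) with a significance of 0.05 and a power of 0.8". Attrition is put at 10%.

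**The concern.** The article identifies two features of the person with dementia as typical sources of caregiver burden. It measures a counterpart of each at baseline and uses neither in the primary model. As far as the article says, randomisation does not balance them either.

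In a linear model of a randomised comparison, a prespecified covariate that predicts the outcome shrinks the residual variance and corrects the estimate for any chance difference between arms in that covariate. If NPI and GDS predict the 3-month CarerQol-7D beyond its own baseline value, the planned model leaves some precision unused. It also leaves the single trial that will be run more exposed to chance imbalance in these two variables.

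**Working it through.** **Inputs from the article.** 144 dyads allocated 1:1; standardised effect 0.5; two-sided alpha 0.05; power 0.80; attrition 10%; baseline CarerQol-7D the only covariate.

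**Inputs assumed, because the article gives neither.**
- ρ, the correlation of baseline with 3-month CarerQol-7D: 0 and 0.5.
- R², the share of the variance left after baseline CarerQol-7D that NPI and GDS together explain: 0.02 to 0.20.

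**Step 1: the plan's own figure.** A two-sample t-test with d = 0.5, alpha 0.05 and power 0.80 needs 63.8, so 64 per arm. Then 64/(1 − 0.10) = 71.1, so 72 per arm and 144 in total. This matches exactly and uses no covariate adjustment.

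**Step 2: dyads analysed.** 144 × 0.90 = 129.6, taken as 130.

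**Step 3: power of the planned and the extended model.** With the baseline score in the model, regressing change or the 3-month score gives the same group coefficient, so the effect is taken as 0.5 SD of the 3-month score.

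- Residual SD = √(1 − ρ²) × √(1 − R²), with R² = 0 for the planned model.
- Noncentrality = 0.5 / (residual SD × √(4/130)).
- Degrees of freedom: 130 − 3 = 127 for the planned model and 130 − 5 = 125 with NPI and GDS as one term each.
- Reduction in standard error = 1 − √(1 − R²). Equivalent number of dyads = 130/(1 − R²).

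Example with ρ = 0.5 and R² = 0.10: residual SD = 0.866 × 0.949 = 0.822; noncentrality = 0.5/(0.822 × 0.1754) = 3.47; power 93.1%.

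| R² (assumed) | SE reduction | Equivalent dyads | Power, ρ = 0 | Power, ρ = 0.5 |
|---|---|---|---|---|
| planned model | – | 130 | 80.8% | 90.4% |
| 0.02 | 1.0% | 133 | 81.5% | 91.0% |
| 0.05 | 2.5% | 137 | 82.7% | 91.8% |
| 0.10 | 5.1% | 144 | 84.6% | 93.1% |
| 0.15 | 7.8% | 153 | 86.6% | 94.3% |
| 0.20 | 10.6% | 163 | 88.5% | 95.5% |

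**Step 4: cost if the covariates explain nothing.** With R² = 0 and 125 degrees of freedom, power goes from 80.75% to 80.74% at ρ = 0, and from 90.43% to 90.42% at ρ = 0.5. The loss is about 0.01 percentage point.

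**Step 5: chance imbalance.** With 65 per arm, the standardised difference in a baseline covariate has SD √(4/130) = 0.175, so 95% of randomisations fall within 1.96 × 0.175 = 0.34 SD. Treat NPI and GDS as one combined score, uncorrelated with baseline CarerQol-7D. At that limit, leaving the score out shifts the estimate by 0.34 × √R² × √(1 − ρ²). For ρ = 0.5 and R² = 0.02, 0.05, 0.10 and 0.20 this is 0.04, 0.07, 0.09 and 0.13 outcome SD, against a design effect of 0.5.

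**Step 6: validity of the planned model.** A simulation used 20,000 replicates of 130 dyads with ρ = 0.5 and one added covariate with R² = 0.10. Type I error was 4.8% with the baseline score alone and 4.9% with the covariate added. For a true effect of 0.5, the mean estimate was 0.498 under both models.

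**The case against.** The strongest reply is that nothing here is wrong. Adjusting for the baseline outcome is a standard, valid primary analysis. It holds its type I error, is unbiased over randomisations and already includes a natural prognostic covariate. All of that stands. Four stronger readings are tempting, and the article supports none of them.

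- **That precision is definitely lost.** The article gives no correlation of NPI or GDS with CarerQol-7D. The Background speaks of burden, not of the 3-month CarerQol-7D, and baseline CarerQol-7D may already carry much of the effect. Excluding people with aggressive or wandering behaviour may also narrow the NPI range. The gain could be close to zero.
- **That the trial has 80% power and nothing in reserve.** This is so only if baseline CarerQol-7D explains nothing. The 144 comes from an unadjusted calculation, so the planned baseline adjustment is itself a reserve.
- **That symptoms and cognition are said to drive nursing home placement, and hence missing data.** The Background sentence attributes the placement risk to the caregiver's burden. The Missing data section plans multiple imputation when data are judged missing at random, and NPI and GDS can serve in an imputation model without being in the primary regression. Their use there would be analysis-plan detail, and that plan is not shown.
- **That nothing balances these variables.** A condensed article that names no stratification factor does not show that there is none.

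It is also fair to ask why these two and not a caregiver measure such as CES-D or hours of care. The answer is only that the article's own rationale points to these two. That is enough for a suggestion, but it does not show that they are the best choice.

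**Conclusion.** The planned model is sound and the sample size stands. What remains is an efficiency improvement that uses data already being collected. If NPI and GDS explain 2% to 20% of the variance left after baseline CarerQol-7D, power rises by 0.7 to 7.7 points at ρ = 0 (81.5 − 80.8; 88.5 − 80.8), or by 0.6 to 5.1 points at ρ = 0.5 (91.0 − 90.4; 95.5 − 90.4). Protection against chance imbalance improves on the same condition. Both ranges rest on assumed values of R² and ρ and on 10% attrition. If R² is zero nothing is gained, and practically nothing is lost.

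**What to change.** In Outcome analysis, extend the description of the primary model to: *adjusting for baseline CarerQol-7D, baseline NPI total and baseline GDS*. Fix this before any outcome data are seen, because covariates added after an imbalance has been noticed would look data-driven. State in advance how GDS enters; the figures above assume one linear term. Report the model with baseline CarerQol-7D alone as a check.

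The cost is one line of text and about two degrees of freedom out of 127. It needs no new data and no change to the 144. If the sponsor prefers to keep the present primary model, the extended model can be prespecified as a sensitivity analysis, though the primary test then gains no precision.

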**Methods:**

A randomized controlled study design will be used, comparing an intervention group with a control group. The intervention will last for five days and will be delivered in either a holiday park or a bed and breakfast setting. The control group will receive care as usual. Data will be collected at baseline and after 3 and 6 months, and outcomes will be assessed in the caregiver group and in the dementia group. The primary outcome will be caregiver-related quality of life after 3 months. The main secondary outcome will be the neuropsychiatric symptoms in the dementia group. Secondary outcomes in the dementia group will be activities of daily living and instrumental activities of daily living, use of health facilities, quality of life, agitation, dementia severity, and use of psychotropic medication. Secondary outcomes in the caregiver group will be the subjective and objective burdens, health and health care facility use, psychotropic medication use, depression, anxiety, and perseverance time.

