## Methods

### Study design

A randomized controlled trial study design will be used (registered at the Dutch Trial Register; Trial ID, NTR5775). After providing informed consent, participant dyads (caregiver and a person with dementia) will be randomly assigned to an intervention or a control group. In the intervention group, participant dyads will take part in the training program (entitled “More at Home with Dementia”), while in the control group, participants will receive care as usual. Data will then be collected at three points: at baseline and during meetings at 3 and 6 months after the intervention. Additionally, information on the use of care and health facilities will be collected by telephone after 6 and 18 weeks. People who drop out of the intervention or control group will be contacted at regular times by phone to request information on the date of admission to a nursing home or death, as applicable.

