#### Setting

The intervention will last for a total of five days and will take place at either a holiday park (https://www.zuytlandbuiten.com/) or a bed and breakfast (https://www.deappelgaard-gouderak.nl/) near Rotterdam. Accommodation will be provided to host six couples, each with their own bedroom. Groups will then consist of three to six participant dyads.

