#### Program for caregivers

The caregivers will attend 14 psycho-educational sessions. These will be delivered in an informal setting by a psychologist, a physiotherapist, an occupational therapist, an elderly care physician, a speech therapist, a dietician, and a social worker. Sessions will include didactic elements, group work, modeling, and role play, as follows:*Combating social isolation.* Participants will be stimulated to share their experiences and to explore available social contacts, support and needs. An open and supportive relationship can be established between caregivers during the intervention and subsequent meetings.*Medical aspects of dementia.* Relevant information will be provided about the types of dementia and associated changes in behavior, as well as accompanying symptoms like apraxia and aphasia. Frequently occurring complications like delirium and depression will be explained.*Planning for the future.* The need to plan for future emergencies and unforeseen events will be discussed, including driving, legal and financial matters, and advance care directives. The issues will be explored during the sessions, but participants will be advised to explore them further at home, preferably with their partner, and if necessary with the help of relatives or professionals.*Re-rolling.* This session will explore issues regarding changes in the roles and responsibilities of the caregiver and the person with dementia. Caregivers will be assisted in considering ways to take over tasks from the people with dementia while preserving their dignity. Attention will then be paid to how to deal with new responsibilities.*Reminiscence and orientation.* Caregivers will be provided with information on techniques that encourage reminiscence (e.g., life history book, music, objects representing notable events) and orientation to the environment and reality (e.g., signs and clocks designed for people with dementia).*Communication.* Information will be given about aphasia and how it affects communication, together with management strategies. Attention will be paid to problems with swallowing.*Assertion.* It will be important to provide training about assertive, non-assertive, and aggressive behaviors, and to provide strategies to cope with criticism. The rights of caregivers should be emphasized and observed, and their needs should be heard and met.*Therapeutic use of activities.* We will identify meaningful and enjoyable activities that are increasingly difficult for the people with dementia to perform. Caregivers will be taught a method of activity analysis that will enable them to break these activities down into component steps and modify or eliminate steps that cannot be completed.*Organization of work and safety in the home.* This session will focus on simplifying, prioritizing, and using outside assistance to achieve a better balance between work and leisure. Attention will be paid to safety at home.*Nursing skills.* Issues associated with dementia will be discussed, such as incontinence, personal care, medication, and mobility. Caregivers will be educated about how to give personal care to a nursing standard, focusing on washing, assistance with dressing, assistance with rising from a chair or bed, and managing incontinence.*Fitness.* The benefits of exercise for both the caregiver and the person with dementia will be emphasized. If possible, exercises or walks will be included in the program. In case of disability, alternatives to walking will be discussed.*Nutrition.* Attention will be paid to the changes in diet, food intake, food preferences, and nutritional needs of people with dementia. Caregivers will be given advice about how to deal with these issues and about how to improve the eating experience.*Self-care.* Caregivers will be given the opportunity to identify their support needs. Attention will also be paid to stress management and relaxation techniques.*Using community services.* Information will be distributed about the many support services that are available (e.g., day care and support at home) and about how to access them. Special emphasis will be given to the financial costs of these services for the couple.

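### The per-protocol set can filter only the intervention arm, because controls have no program to complete, so the complement to the ITT result loses the protection of randomisation

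*Protocol article*

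**What the plan says.** The Outcome analysis section of the protocol article sets the roles of the two analyses of the primary outcome: "We will perform a primary intention-to-treat analysis for the primary equation, which will be complemented with a secondary per-protocol analysis". The ITT set is complete: "The intention-to-treat population will include all information from participants randomized to each treatment arm". The per-protocol set is restricted: "the per-protocol population will only include information about those who completed the program to which they were allocated". The only stated covariate in the primary model is the baseline outcome score.

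The arms differ in what there is to complete.

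- Intervention: "The intervention will last for a total of five days" (Setting), and "The caregivers will attend 14 psycho-educational sessions" (Program for caregivers).
- Control: "while in the control group, participants will receive care as usual" (Study design); the abstract says the same, "The control group will receive care as usual".

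On timing, Study design states: "After providing informed consent, participant dyads (caregiver and a person with dementia) will be randomly assigned to an intervention or a control group". Allocation therefore precedes the program. Nothing in the article says what completion would mean for a control dyad.

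**The concern.** Completing the program is an event after randomisation that can be observed in only one arm. Intervention dyads who do not start or finish are dropped. The control dyads who would have behaved in the same way cannot be identified and stay in. The two groups compared are then no longer those that randomisation made alike.

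The analysis concerns the primary outcome, and the trial is meant to inform introduction of the program into routine care. A reader may well take the per-protocol figure as the effect of actually receiving the program. As defined, it does not estimate that effect without a strong and untestable assumption about who fails to complete.

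**Working it through.** **1. The rule applied to each arm.**

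| | Intervention | Control |
|---|---|---|
| Program allocated | Five-day residential stay, 14 caregiver sessions | None; usual care |
| Can a dyad fail to complete it? | Yes | No |
| Literal reading of the rule | Non-completers removed | Every dyad removed, which cannot be meant |
| Workable reading | Non-completers removed | Nobody removed |
| Alternative: controls must complete follow-up | Filtered on the program | Filtered on study retention |

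The workable reading gives one-sided exclusion. The alternative filters the arms on different criteria. Neither restores comparability.

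**2. The plan's own figure, used only as a yardstick.** Sample size calculation gives a standardised effect of 0.5, significance 0.05, power 0.8, 10% attrition and 144 couples. A two-sided two-sample t-test needs 64 per arm; 64 / 0.9 = 71.1, rounded up to 72; 2 x 72 = 144. The figure reproduces and is not in dispute. The 10% is attrition from the study, not a rate of program non-completion.

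**3. Shift from one-sided exclusion.** Let q be the share of the intervention arm that is excluded, and g the number of SDs by which those dyads would score worse than completers whatever their allocation, after adjustment for baseline CarerQol-7D. Write C for the completers' mean. With no true effect, both full arms have mean

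(1 - q) x C + q x (C - g) = C - q x g.

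The restricted intervention arm has mean C, so the contrast shifts by C - (C - q x g) = q x g.

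The document gives neither q nor g. Both are assumed below. The share of 0.5 assumes that g is in the same SD units as the planned effect.

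| q | g | Shift q x g | Share of 0.5 | Simulated two-sided type I error |
|---|---|---|---|---|
| 10% | 0.5 | 0.05 SD | 10% | about 5.5% |
| 20% | 0.5 | 0.10 SD | 20% | about 9% |
| 10% | 1.0 | 0.10 SD | 20% | about 8% |
| 20% | 1.0 | 0.20 SD | 40% | about 18% |

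The simulation used 8,000 runs, 72 dyads per arm before exclusion, a nominal 5% level and no baseline covariate, so its SD stands for the residual SD. When the same kind of dyad was removed from both arms, the shift was about 0 and the error about 5%. The one-sidedness, not the loss of numbers, is what does the harm.

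**4. Against sampling error.** With 64 per arm the standard error of the difference is sqrt(2/64) = 0.177 SD. A shift of 0.05 is 0.05 / 0.177 = 0.28 standard errors, and 0.10 is 0.57. The lower case is small; the upper is not negligible.

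**5. What the alternative does.** If no control receives the program, the CACE is the ITT effect divided by the share that starts it. With a true effect of zero it is centred on 0 / share = 0, whatever the prognosis of the non-starters. Treating the share as known, the interval widens by 1 / 0.9 = 1.11 if 10% never start, and by 1 / 0.8 = 1.25 if 20% never start (assumed shares).

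**The case against.** **ITT is primary and the per-protocol analysis is labelled secondary.** This stands. No decision rule or sample size rests on the per-protocol result. A reader might infer that the trial's main conclusion or its type I error is compromised. It is not, because the ITT set keeps everyone randomised; the error rates above concern the per-protocol test alone.

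**Completion thresholds and adherence rules usually belong in the analysis plan.** True of the detail, and a missing threshold is not the point. The article does state the inclusion rule, and a numerical threshold for the intervention arm would not make it applicable to controls.

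**Study design foresees dropout from both arms, so a control-side criterion may be intended.** Possible, but that is dropout from the study, not completion of a program. If it was meant, the arms are selected on different events.

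**The direction is unknown.** This stands. It is tempting to say that the analysis favours the intervention by construction. The document does not support that. Non-completion might reflect low need, logistics or intercurrent illness as easily as heavy burden, and the eligibility criteria already exclude people with dementia who show aggressive or wandering behaviour. Only the one-sided exclusion is structural; the sign is a plausible guess.

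**Baseline adjustment may absorb the selection.** In part. Only a gap that remains after adjustment for baseline CarerQol-7D causes bias, and the illustration is defined that way. The baseline score need not capture a change in behaviour away from home, or a caregiver's illness after allocation.

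**A CACE adds little.** With one-sided non-compliance it tests essentially the same null hypothesis as ITT, so it is not independent evidence. It does answer the question of receipt without discarding randomised dyads.

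**Conclusion.** The point holds for the secondary per-protocol analysis of the primary outcome. As defined, its population can be applied meaningfully only to the intervention arm, so the comparison is not protected by randomisation. It is unbiased only if non-completion is unrelated to the 3-month CarerQol-7D given its baseline score, and nothing in the article supports that assumption.

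Upward bias is plausible if more burdened dyads fail to finish. With assumed non-completion of 10-20% and an assumed residual gap of 0.5 SD, the shift is 0.05-0.10 SD. This shows scale and is not an estimate; a gap of zero gives no bias and a gap in the other direction reverses the sign. The change should be made, but the primary ITT analysis stands without it.

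**What to change.** Replace the per-protocol analysis as the complement to ITT. Suggested content:

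- Estimate the complier average causal effect on change in CarerQol-7D at 3 months by two-stage least squares, with randomised allocation as the instrument and baseline CarerQol-7D as a covariate in both stages.
- Keep all randomised dyads in the arm to which they were allocated, and handle missing outcomes as in the ITT analysis.
- Define receipt in advance as having started the five-day program. A minimum number of the 14 sessions is a weaker choice: dyads below the cut-off may still benefit, and dividing by the share above it would then overstate the effect.
- If a per-protocol table is kept, label it descriptive, state the criterion used in each arm, and draw no inference from it.

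The cost is a change of wording, a standard analysis and a record of attendance for each dyad. There are three downsides to state in the plan. The interval is wider than for ITT. The estimate relies on the exclusion restriction, that is, allocation has no effect on dyads who do not start the program. And it is the effect of starting the program, not of finishing every session.
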